# Telemedicine Versus Standard Follow-Up Care for Diabetes-Related Foot Ulcers: Protocol for a Cluster Randomized Controlled Noninferiority Trial (DiaFOTo)

**DOI:** 10.2196/resprot.5646

**Published:** 2016-07-18

**Keywords:** diabetes, diabetic foot, foot ulcer, telemedicine, randomized controlled trial, primary care, delivery of health care, integrated, complex intervention, patient-reported outcomes, Norway, cluster RCT

## Abstract

**Background:**

This paper presents the protocol for an ongoing study to evaluate a telemedicine follow-up intervention for patients with diabetes-related foot ulcers. Diabetes-related foot ulcers represent challenges for patients and the health services. The large increase in the prevalence of diabetes, combined with the aging population, means that the absolute number of patients with diabetes-related foot ulcers is likely to continue to increase. Health care services therefore need to provide close clinical follow-up care for people with diabetes both in primary and specialist care. Information and communication technologies may enable more integrated treatment and care pathways across organizational boundaries. However, we lack knowledge about the effect of telemedicine follow-up and how such services can be optimally organized.

**Objective:**

To present the design and methods of a study evaluating a telemedicine follow-up intervention for patients with diabetes-related foot ulcers.

**Methods:**

The study is designed as a cluster randomized controlled trial (noninferiority trial) involving municipalities or municipality districts (clusters) belonging to one clinical site in Western Norway. The study includes patients with type 1 and type 2 diabetes presenting with a new foot ulcer at the initial visit to the clinic. Patients in the intervention group receive telemedicine follow-up care in the community. The key ingredient in the intervention is the close integration between health care levels. The intervention is facilitated by the use of an interactive wound platform consisting of a Web-based ulcer record combined with a mobile phone, enabling counseling and communication between nurses in the community and specialist health care. Patients in the control group receive standard hospital outpatient care. The primary endpoint in the trial is healing time; secondary outcomes include amputation and death, patient-reported outcome measures, and follow-up data on the recurrence of foot ulcers. In addition, qualitative substudies are being performed to provide a more comprehensive evaluation of the ongoing processes during the trial with the patients in the intervention and control groups and those health care professionals either working in primary care or in specialist care delivering the intervention.

**Results:**

The project has been funded. The inclusion of patients started in September 2012. Because recruitment goals were not met in the initial period, two more clinical sites have been included to meet sample size requirements. Patient recruitment will continue until June 2016. Data collection in the qualitative substudies has been completed.

**Conclusions:**

This telemedicine trial operates in a novel setting and targets patients with diabetes-related foot ulcers during a 12-month follow-up period. The trial addresses whether integrated care using telemedicine between primary and specialist health care can be an equivalent alternative to standard outpatient care.

**Trial Registration:**

ClinicalTrials.gov NCT01710774; https://clinicaltrials.gov/ct2/show/NCT01710774 (Archived by WebCite at http://www.webcitation.org/6im6KfFov).

## Introduction

### Background

The prevalence of diabetes is expected to increase both in Norway and globally [1]. In Norway, about 200,000 people have been diagnosed with diabetes [2] with an annual increase of 8000 to 10,000 forecast. In addition, an estimated 150,000 people have undiagnosed type 2 diabetes [2,3]. The increasing prevalence of diabetes, especially type 2 diabetes, combined with an increasing proportion of older people in the population present great challenges for the health care services [2,4,5]. An epidemiologic study of diabetes-related foot ulcers among community-dwelling adults and older people based on data from the Nord-Trøndelag Health Study (HUNT2) showed that a history of foot ulcer was significantly associated with increased mortality and that about 10% of people with diabetes reported a history of foot ulcer [6-8]. Other studies have shown that a foot ulcer is associated with reduced quality of life, social limitations, and pain [9]. The cost of treating foot ulcers is also considerable [10]. It is therefore important to start treatment early and have a close, well-organized follow-up for patients with diabetes-related foot ulcers to improve the management of the diabetic foot [11].

### State of the Evidence, Relevance, and Innovation Potential

The main goal for the Norwegian Coordination Reform in the health care sector in January 2012 was to obtain coordinated and integrated health care for patients, especially for those with complex conditions [12]. In this reform, electronic communication and use of telemedicine is emphasized. Qualitative studies of diabetes-related foot ulcers [13-15] have shown that using telemedicine can result in follow-up care of similar quality to standard outpatient care while at the same time enabling more flexible organization and greater patient satisfaction. Patients with diabetes foot ulcers are prone to adverse outcomes because of rapid deterioration of the ulcer or the onset of infection. To date, randomized controlled studies have not confirmed that telemedicine follow-up care for patients with diabetes-related foot ulcers results in equivalent healing time when compared with standard outpatient care in specialist health care [16,17]. Therefore, there is a need for such studies to document the safety and effectiveness of a telemedicine-based follow-up. This project is expected to increase the focus on research related to integrated care [3,12].

This paper presents the protocol for an ongoing cluster randomized controlled noninferiority trial, DiaFOTo (Diabetic Foot and Telemedical Images Project). The trial is designed to compare the effect of telemedicine follow-up in primary care to standard hospital outpatient care on ulcer healing time. In addition, qualitative data were collected to evaluate ongoing processes and further elaborate the experiences of patients and health care professionals during the intervention period. These qualitative studies are part of a larger program supported by the Norwegian Research Council (DiaHEALTH-221065/F40) to promote patient and professional competencies in diabetes care and management.

### Aims and Research Questions

The main aim of this trial is to evaluate whether follow-up of patients with diabetes-related foot ulcers in primary care, in collaboration with hospital outpatient specialist care, is noninferior to standard outpatient care in terms of ulcer healing time.

Our primary research question is whether healing time (within 12 months) of diabetes-related foot ulcers treated in primary care in collaboration with telemedicine consultations with a hospital outpatient is no worse than with standard hospital outpatient care. The corresponding null hypothesis: mean difference in healing time is 1.5 months or less for diabetes-related foot ulcers with telemedicine follow-up in primary care, compared to standard hospital outpatient care.

We will also evaluate whether the incidence of amputation and mortality, sickness absence, clinical measures (number of consultations, complications directly related to the foot ulcer as indicated by use of antibiotics), recurrence of a new foot ulcer (within 48 months), and patient-reported outcome measures (PROMs) are different for telemedicine follow-up in primary care compared with standard hospital outpatient care.

We conducted supplementary qualitative studies to provide a more comprehensive description and evaluation of the ongoing processes during the intervention. Individual interviews with patients in the intervention and control groups aimed to explore patient experiences with telemedicine follow-up or standard outpatient care delivered in the DiaFOTo trial. Focus group interviews with health care professionals either working in primary care or in specialist care delivering the intervention aimed to explore health care professional experiences when they adopt this new technology in caring for patients with diabetes foot ulcers.

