### Sample Size

A statistical power analysis based on the primary outcome measure (healing time) was performed to decide the number of participants to be included using PASS sample size software, version 11 (NCSS, LLC). We powered the study to detect a difference in mean healing time larger than the selected noninferiority margin of 1.5 months [44,45], assuming 80% power, a significance level of .025, and a standard deviation of 3.6 months [46]. The analysis showed that on an individual level, a total sample size of 184 is needed. Considering an intraclass correlation coefficient of .02 and an average cluster size of 10 participants (design effect of 1.18), this number increased to 217 participants. As we expect an attrition rate of 5%, we aim to include 114 patients in each treatment group.

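### The stated null hypothesis is the noninferiority claim itself, and the lower-limit decision rule carries the reversal into the primary conclusion

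*Protocol article*

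**What the plan says.** Three places in the article bear on this point.

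- **Aims and Research Questions.** The main aim is to show that telemedicine follow-up "is noninferior to standard outpatient care in terms of ulcer healing time". The research question that follows is consistent with this. The hypothesis statement then reads: "The corresponding null hypothesis: mean difference in healing time is 1.5 months or less for diabetes-related foot ulcers" followed up by telemedicine, relative to standard care.
- **Sample Size.** "We powered the study to detect a difference in mean healing time larger than the selected noninferiority margin of 1.5 months", "assuming 80% power, a significance level of .025, and a standard deviation of 3.6 months". The assumed true difference is not given, nor is it said whether the level is one-sided or two-sided.
- **Statistical Analysis.** Telemedicine is to be declared noninferior when the lower bound of the 95% interval for the difference in mean healing time falls under 1.5 months. The direction of subtraction is not stated.

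Nowhere does the article give the opposite null (a difference of 1.5 months or more) or a rule based on the upper limit.

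**The concern.** A noninferiority test takes as its null that the new treatment is worse by the margin or more, and claims success by rejecting it. The significance level then caps the risk of accepting an unacceptably worse treatment. Here the null is the region of acceptable results. Rejecting it would show inferiority, and the .025 level would cap the risk of falsely declaring inferiority.

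The hypothesis sentence alone could be a slip. What gives it force is the decision rule: a lower limit below 1.5 is exactly non-rejection of a null of 1.5 or less. Noninferiority is then concluded from absence of evidence of inferiority, and a smaller or noisier trial passes more easily. That is a practical worry here, because the Results section reports that early recruitment fell short and two hospitals had to be added.

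**Working it through.** **Inputs.** Margin 1.5 months, SD 3.6 months, 80% power, level .025, 184 individuals, ICC .02, cluster size 10, design effect 1.18, 217 after clustering, all from Sample Size. The decision rule is from Statistical Analysis. The difference D is telemedicine minus standard care, so a positive D means slower healing with telemedicine.

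**1. Reproduce the plan's figure** ("on an individual level, a total sample size of 184 is needed"). Normal approximation, true D = 0, one-sided .025:

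n per arm = 2 × (1.960 + 0.842)² × 3.6² / 1.5² = 2 × 7.85 × 5.76 = 90.4, so 91 per arm, 182 in total.

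The noncentral t calculation gives power 0.798 at 91 per arm and 0.803 at 92, hence 184. A two-sided .025 level would need about 220, so .025 is the level in one tail. The design effect is 1 + 9 × 0.02 = 1.18, and 184 × 1.18 = 217.1, as stated.

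**2. What 184 can and cannot show.** The calculation depends only on the distance of 1.5 months between the tested value and the assumed truth. At 92 per arm, power is 0.803 for each of:

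- null D ≥ 1.5, truth D = 0 (correct noninferiority test);
- a two-sided .05 superiority test of a 1.5-month difference;
- null D ≤ 1.5, truth D = 3.0 (the reversed test).

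So 184 does not identify which hypothesis was used.

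**3. Precision.** 217 / 1.18 = 183.9, or about 92 effective patients per arm. SE = 3.6 × √(2/92) = 0.531 months, and 1.96 × 0.531 = 1.040.

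**4. Largest observed difference that passes.**

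- Upper limit below 1.5: observed D below 1.5 − 1.040 = 0.46 months.
- Lower limit below 1.5, as stated: observed D below 1.5 + 1.040 = 2.54 months.

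**5. Probability of declaring noninferiority** (normal approximation), Φ((threshold − D)/SE):

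| True D (months) | Upper-limit rule | Stated lower-limit rule |
|---|---|---|
| 0 | 80.7% | about 100% |
| 1.5 | 2.5% | 97.5% |
| 2.0 | 0.2% | 84.6% |
| 2.5 | below 0.1% | 53.0% |
| 3.0 | below 0.1% | 19.3% |

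The 80.7% differs from the 80.3% in step 1 only because it uses the normal in place of the t distribution.

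**6. Effect of a smaller trial.** With half the effective size, 46 per arm, SE = 3.6 × √(2/46) = 0.751, and the stated rule would pass any observed difference below 1.5 + 1.96 × 0.751 = 2.97 months. Less information makes success easier.

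**7. Sign convention.** If the difference were standard minus telemedicine, the correct null would be a difference of −1.5 or less, and the correct rule a lower limit above −1.5. Neither is what the article says, so reversing the subtraction does not repair the text.

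**The case against.** The strongest reply is that this is a drafting error in a trial that is otherwise properly conceived. The aim and research question are worded correctly, the power sentence names a noninferiority margin, the level is .025, and the numbers fit a standard noninferiority calculation. Much of this stands. The power sentence in particular is loose wording and weak evidence on its own.

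The reply does not reach the decision rule. A misworded null would matter little beside a correct rule for success, but the rule has the same direction as the misworded null, and nothing in the article overrides it. Nor is this a detail left to an analysis plan: the article chose to state the null and the rule, and stated both wrongly.

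Three stronger readings are tempting and should be resisted.

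- A reader might infer that 184 can arise only from the correct hypotheses, so that text and number contradict each other. Step 2 of the working shows otherwise.
- A reader might infer that the null sentence and the power sentence alone produce a 97.5% error. They do not, because neither says that non-rejection counts as success. That figure comes from the rule in Statistical Analysis.
- A reader might infer that the sample size is wrong or that the data will in fact be analysed backwards. The article supports neither. It shows what is written, not what the trial team will run.

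**Conclusion.** The point holds in this form: the null is stated as the noninferiority claim, the power sentence describes detecting rather than excluding a difference beyond the margin, and the decision rule amounts to failing to reject that reversed null. Applied as written, the rule would declare noninferiority about 97.5% of the time at a true difference equal to the margin, where 2.5% is intended, and would pass observed differences up to about 2.54 months, not 0.46.

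These figures assume the planned SD of 3.6 months, about 92 effective patients per arm after the design effect, and a difference taken as telemedicine minus standard care. The 97.5% at the margin follows from the 95% interval and does not depend on the SD or sample size; the observed-difference thresholds do. The planned numbers can stand, since they agree with a correct calculation at a true difference of zero. Because the error sits in the criterion for the primary conclusion, it should be corrected before the primary analysis.

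**What to change.** Change three sentences together. Correcting the first two alone would leave the operative rule reversed.

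- **Aims and Research Questions:** H0: mean healing time, telemedicine minus standard care, ≥ 1.5 months; H1: < 1.5 months.
- **Sample Size:** 80% power at one-sided .025 to exclude a difference of 1.5 months or more when the true difference is zero.
- **Statistical Analysis:** noninferiority is confirmed only if the upper limit of the 95% confidence interval for telemedicine minus standard care is below 1.5 months.

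The cost is wording only. The 184 individuals, the 217 after clustering and the recruitment target of 114 per group do not change, and no new data are needed. The trial team should confirm the true difference assumed in the original calculation, since the article does not state it. The correction should be on record before the outcome data are analysed; the article expects to present results in 2017.

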## Methods

### Trial Design

In this pragmatic randomized controlled trial (RCT) [18], we evaluate the effectiveness of the intervention on patient health using the Model for Assessment of Telemedicine criteria [19] and the complex intervention framework developed by the Medical Research Council in the United Kingdom [20]. We used a noninferiority parallel cluster design. The flow and attrition diagram is shown in Figure 1 and based on the CONSORT 2010 statement: extension to cluster randomized trials [21]. Reporting will adhere to the guidelines of the Consolidated Standards for Reporting Trials (CONSORT) [22]. The trial is in accordance with the CONSORT EHEALTH checklist [23]. The study has been registered with ClinicalTrials.gov [NCT01710774].

Quantitative data are being collected at the time of inclusion (baseline) after informed consent has been obtained and before randomization (t1), and the patient is monitored every second week until the foot ulcer has either healed or until the end of follow-up (maximum 12 months after baseline) (t2). Additional information will be retrieved 36 months after the initial follow-up period about the occurrence of new foot ulcers, amputation, or death. Maximum follow-up for each patient is therefore 48 months.

**Figure 1 figure1:**
[figure not shown]
Flow diagram of clusters and patients in the cluster randomized controlled noninferiority trial, DiaFOTo.

### Trial Population and Recruitment

We are currently including all patients with diabetes-related foot ulcers from the southern part of Rogaland County referred to the endocrinology unit of Stavanger University Hospital (Stavanger HF) between September 2012 and June 2016 at the initial visit to the clinic.

The trial includes patients with type 1 or type 2 diabetes if they are 20 years or older and present a new foot ulcer to the clinical site. A foot ulcer is defined as a skin lesion below the ankle on a diabetic foot. The exclusion criteria include (1) an ulcer on the same foot treated during the past 6 months in specialist health care (because chronic ulcers can interfere with the primary outcome in the study protocol); (2) mental disorders or cognitive impairment (including schizophrenia, other psychotic disorders, and dementia); (3) inability to complete questionnaires in Norwegian, or (4) life expectancy of less than 1 year. Patients are being assessed for primary diagnosis and treatment at the clinical site according to standard protocols based on national guidelines [3].

### Randomization and Blinding

The southern part of Rogaland County in the western part of Norway was divided into 26 clusters based on municipalities or districts within municipalities. These were matched in pairs according to population size and rural/urban characteristics. Within each of the 13 pairs, the two clusters were randomly allocated to intervention or standard treatment. The randomization sequences were generated by an independent person using SPSS version 21 statistical software (IBM Corp). All patients in each cluster/municipality are in the same treatment group. All participants are informed by the study nurse about the allocated type of treatment after enrollment in the study and after providing baseline data. The intervention is designed to evaluate a change in health service provision; therefore blinding of the intervention is not possible. The study staff monitors whether pictures are submitted as planned and follows up to ensure compliance. We also assess how closely the nurses follow the protocol. The outcome is assessed by health care professionals at the outpatient clinics, who are not blinded to study arm but are trained to follow and assess wounds using a standardized protocol. The numbers of patients who do not meet the inclusion criteria, decline to participate, or drop out of the trial are recorded by age and gender.

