### Statistical Analysis

We will report descriptive statistics of baseline characteristics for the treatments groups including means and standard deviations (medians and interquartile ranges for continuous variables and numbers and percentages for categorical variables).

Noninferiority of the telemedicine intervention will be confirmed if the lower limit of the 95% confidence interval for the mean difference in healing time is less than 1.5 months. To account for correlated data introduced by the study design, we will apply the linear mixed-effects model [47] for this analysis. In addition, we will analyze group differences in time to healing with a proportional hazards model with adjustment of the standard error for clustered observations. Secondary outcome measures will be analyzed with superiority hypothesis tests. These tests will be based on either (generalized) mixed-effects models [47] or proportional hazards models (cluster) depending on the type of the outcome measure investigated. Estimated effect measures (absolute and relative) will be presented with 95% confidence intervals and *P* values.

Because our trial has a maximum follow-up period of 48 months, we expect some dropouts. We will perform intention-to-treat analyses and additional analyses based on the participants who actually participated actively in our trial during the 12-month follow-up period.

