## Results

The study has been successfully funded. The inclusion of patients started September 2012 from 26 municipalities or districts. Because recruitment goals were not met in the initial period, two more hospitals from the Western Norwegian Health Region have been included to meet sample size requirements. Patients from Sunnhordland County referred to the department of surgery at Stord Hospital (Helse Fonna HF) were included from September 2013 (6 districts), and patients from Hordaland County referred to the department of orthopedics or endocrinology unit at Haukeland University hospital (Helse Bergen HF) were included from November 2014 (10 districts), for a total of 42 districts before randomization (Figure 1). Furthermore, patient recruitment has been extended through June 2016. We expect to present results of the study in 2017.

Data collection in the qualitative substudies has been completed. Information on patient experiences was collected between March 2014 and May 2015 from 24 participants with diabetic foot ulcers receiving either the telemedicine follow-up in primary care in collaboration with outpatient specialist care or standard outpatient care. Information on health care professional experiences was collected through 10 focus group interviews from 7 home-based care services, 2 outpatient clinics, a medical center, and a nurse-led primary care clinic during 2014 and 2015 (n=43). Focus group interviews lasted from 70 to 90 minutes, included 3 to 7 health care professionals, and were audiotaped. The results of these studies are submitted and will be available in 2016.

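### No stated analysis names clinical site, although two hospitals working through different departments joined later; adjusting for site is nearly free, whereas pair terms are a trade-off

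*Protocol article*

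**What the plan says.** For the first site, the Randomization and Blinding section describes 26 clusters and states: "These were matched in pairs according to population size and rural/urban characteristics". It continues: "Within each of the 13 pairs, the two clusters were randomly allocated to intervention or standard treatment".

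The Results section reports that recruitment fell short and that "two more hospitals from the Western Norwegian Health Region have been included to meet sample size requirements". One hospital (department of surgery) brought 6 districts from September 2013. For the other (orthopedics or endocrinology), patients "were included from November 2014 (10 districts), for a total of 42 districts before randomization (Figure 1". The text gives no allocation method for these 16 districts, and the flow diagram is not available here.

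On the primary outcome, the Statistical Analysis section says: "To account for correlated data introduced by the study design, we will apply the linear mixed-effects model". It lists no fixed or random terms. The time-to-healing comparison is to use "a proportional hazards model with adjustment of the standard error for clustered observations". Secondary outcomes get mixed-effects or clustered proportional hazards models. Site, pair and the matching factors are not named in any of these analyses.

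**The concern.** Site could matter to healing time for reasons that the article itself supplies:

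- The Control Group section defines standard care as consultations at one hospital's endocrinology unit, while the added hospitals work through other departments as well. Site may therefore change both the comparator and the case mix.
- Healing is taken from each site's medical records (Table 1) and judged by unblinded outpatient staff (Randomization and Blinding), so site may also affect how the primary outcome is measured.
- The sites opened in 2012, 2013 and 2014, so site is tied to calendar time.

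If districts recruit unequally, the arms can differ in the share of patients from each site. A cluster-adjusted standard error changes the width of the interval but leaves the point estimate where it is. It also does not allow the baseline hazard to differ by site. Any site-mix difference would then sit inside the estimate that is compared with the 1.5-month margin, in either direction. A shift in favour of telemedicine makes a noninferiority claim easier to reach.

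**Working it through.** **Inputs.** From the Sample Size section: margin 1.5 months, SD 3.6 months, power 80%, significance level .025 (taken as one-sided), ICC .02, cluster size 10, design effect 1.18, totals of 184 and then 217, attrition 5%, 114 per group. From Randomization and Blinding and from Results: 26 clusters in 13 pairs, then 6 + 10 more, 42 in all.

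**The plan's own figures.** A noncentral-t calculation with true difference 0 gives 92 per arm, 184 in total. Design effect: 1 + (10 - 1) × .02 = 1.18, and 184 × 1.18 = 217.1. Attrition: 217 / 0.95 = 228.4, or 114 per group. All reproduce. The calculation takes no credit for pairing or site, so adding site to the model does not undermine it.

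**Effect of site mix.** If one site supplies a share of patients that differs between arms by d, and its mean healing time differs from the rest by D months, the unadjusted difference moves by d × D. Neither quantity is in the article, so both are assumed:

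- d = 0.10, D = 1: shift 0.1 month, or 0.1 / 1.5 = 7% of the margin.
- d = 0.20, D = 2: shift 0.4 month, or 0.4 / 1.5 = 27% of the margin.

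**Cost of adjusting for site.** With 42 clusters and two arms there are 42 - 2 = 40 cluster-level degrees of freedom. Three sites use two more, leaving 38. The critical t moves from about 2.021 to 2.024.

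**Effect of adjusting for pairs.** Let f be the share of between-cluster variance that pairs explain (assumed, 0 to 1), K the number of clusters, and m = 217 / K, with equal cluster sizes. Between-cluster variance is .02 × 3.6² = 0.259 and within-cluster variance is .98 × 3.6² = 12.70.

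- Ignoring pairs: SE² = 2 × (0.259 + 12.70/m) / (K/2), with K - 2 degrees of freedom.
- With pairs: SE² = 2 × (0.259 × (1 - f) + 12.70/m) / (K/2), with K/2 - 1 degrees of freedom.
- Power comes from the noncentral t with noncentrality 1.5 / SE.

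| Clusters | Analysis | SE | df | Power |
|---|---|---|---|---|
| 26 | ignoring pairs | 0.523 | 24 | 78.5% |
| 26 | pairs, f = 0 / 0.5 / 1 | 0.523 / 0.504 / 0.484 | 12 | 74.9% / 78.0% / 81.2% |
| 42 | ignoring pairs | 0.509 | 40 | 82.0% |
| 42 | pairs, f = 0 / 0.5 / 1 (all assumed paired) | 0.509 / 0.496 / 0.484 | 20 | 80.1% / 82.0% / 83.9% |

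Pair terms therefore change power by -3.6 to +2.7 points with 26 clusters and by -1.9 to +1.9 points with 42. Ignoring the pairs lowers the nominal one-sided 2.5% error, to 1.7% (26 clusters) or 2.0% (42 clusters) when f = 1, which is conservative.

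**The case against.** The strongest reply is that this is silence in a condensed article. The mixed model is said to deal with correlation arising from the design, and the pairs are part of that design, so the wording is compatible with pair or site effects. Model terms are commonly listed in a full protocol or SAP, neither of which is at hand. This stands for the mixed model: a reader might infer that it accounts for cluster correlation only, but the text does not establish that. It has less force for the proportional hazards model, where the article does name its design adjustment, and that adjustment is to the standard error alone.

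Three other inferences are tempting and not supported:

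- That the added districts were randomised within hospital. The text does not describe their allocation. If it was within site, cluster counts would be balanced and only patient numbers could differ between arms.
- That ignoring the pairs throws away power. Clusters carry 10 × .02 / 1.18 = 16.9% of the variance; removing half of that would appear to raise power from 80% to about 84%. This leaves out the degrees of freedom that pair terms use. Under the same assumption (f = 0.5) the change is from 78.5% to 78.0% with 26 clusters, and nil with 42.
- That the trial has an inflated error rate. A 15-point imbalance with a 1.5-month site difference shifts the estimate by 0.225 month. With SE 3.6 × 2/√217 × √1.18 = 0.531, false noninferiority at the margin would be about 6.2%. That figure is conditional on an assumed imbalance of that size in the favourable direction. Chance imbalance averages out over repeated randomisation, and the article reports no imbalance.

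**Conclusion.** The point holds as a specific, inexpensive improvement to the analysis, not as a demonstrated bias or a loss of power. The article documents three hospitals with different departments and start dates, and no stated analysis names site. Followed as written, the proportional hazards model leaves any between-site difference in the estimate; the mixed model does the same if it is fitted without a site term. The possible shift, 0.1 to 0.4 month against a 1.5-month margin, rests wholly on assumed imbalances and site differences. The case for adjustment does not depend on those values, because the cost is about 2 of 40 cluster-level degrees of freedom.

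Pairing is a separate matter. At ICC .02, with equal cluster sizes and an unknown share of variance explained, pair terms may help or hurt power by a few points, and leaving them out is conservative. They do not belong in the primary model on grounds of power.

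**What to change.** Before the data are analysed, so that the choice cannot depend on results:

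- In the linear mixed model for healing time, include clinical site as a fixed effect and cluster as a random effect, with a small-sample degrees-of-freedom method (Satterthwaite or Kenward-Roger).
- Stratify the proportional hazards model by site and keep the cluster-robust standard errors.
- Apply the same structure to the secondary outcomes.
- State how the 16 added districts were allocated, and whether they were paired.
- Adjust for population size and rural/urban character, or for pair, as a sensitivity analysis only. Pairs formed within a site are nested in it, so fixed pair effects would replace the site effect. Strata by pair would be thin in the hazards model: 217 / 21 gives about 10 patients each, if all 42 districts were paired.
- Claim no power gain from these changes.

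The cost is wording in the analysis plan and about 2 cluster-level degrees of freedom. Patients are recruited through their hospital, so site is already held and no new data are needed.
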